**11.3 Amendments**

Amendments are changes made to the research after a favourable opinion by the accredited METC has been given.

**11.4 Annual progress report**

The site investigator will submit a summary of the progress of the trial to the accredited METC once a year. Information will be provided on the date of inclusion of the first subject, numbers of subjects included and numbers of subjects that have completed the trial, serious adverse events/ serious adverse reactions, other problems, and amendments.

**11.5 End of study report**

The site investigator will notify the accredited METC of the end of the study within a period of 8 weeks. The end of the study is defined as the last patient's last visit.

In case the study is ended prematurely, the site investigator will notify the accredited METC within 15 days, including the reasons for the premature termination.

Within one year after the end of the study, the site investigator will submit a final study report with the results of the study, including any publications/abstracts of the study, to the accredited METC

### **11.6 Public disclosure and publication policy**

The publication rights in regard to the main results of the study, i.e., regarding the primary and secondary objectives, belong to the principal investigator. Additional authors are determined by the volume and quality of data at the remaining investigational centres. All site investigators who hold a role of average importance with respect to the volume and quality of data are taken into account for the publication of the essential results of the study.

Additional publications of the analysis results of all patient data can be originated by the investigator as primary author whose ideas are behind a specific paper. However, he/she must at least hold a role of average importance with respect to the volume and quality of data. However, the decision about primary authorship is made by the principal investigator in consultation with the clinical project manager. The primary author then decides with the principal investigator and the involved investigators on the order of additional authors.

The principal investigator and project coordinator have to decide on the publication of data from just one study centre or a selection of investigational centres. The latter publications might have to wait until the publications based on all data have been written.

The primary author writes all publications. If desired, the primary author is supported by the clinical project manager. Before the release of a publication, it must be constructively reviewed and released by all authors. The sponsor will have the chance to review any abstract, manuscript before submission or presentation.

Every investigator can refuse to become a primary or co-author, exchange his or her authorship with another investigator from his or her investigational centre, or exchange his or her primary authorship with a co-authorship.

## 13. APPENDIX I: Schedule of Events

| PROCEDURE / TEST                                                                                                                             | Enrolment
Randomisation
(± 7 days) | End of mCR program
(T1: 6 months)
(± 14 days) | End of study (T2 :
12 months) (± 14 days) |
|----------------------------------------------------------------------------------------------------------------------------------------------|------------------------------------------|-----------------------------------------------------|----------------------------------------------|
| Patient eligibility                                                                                                                   | ✓                                        |                                                     |                                              |
| Patient Informed Consent                                                                                                              | ✓                                        |                                                     |                                              |
| Patient characteristics:
- Demographic
- Physical
- Medical history
- Risk factors
- Medication
- Indication for CR | ✓
✓
✓
✓
✓
✓               |                                                     |                                              |
| Centre characteristic
- Mobile telemonitoring guidance                                                                             | ✓                                        |                                                     |                                              |
| Maximal ergometer exercise test                                                                                                       | ✓                            | ✓                                       | ✓                                            |
| 12-Lead ECG                                                                                                                           | ✓                            | ✓                                       | ✓                                            |
| Physical examination:
- Weight, Length, BMI, Lean body mass, blood pressure                                                        | ✓                            | ✓                                                   | ✓                                            |
| Clinical Laboratory test:
- Lipid profile, renal function and HbA1C                                                                | ✓                            | ✓                                       | ✓                                            |
| Questionnaires                                                                                                                        |                                          |                                                     |                                              |
| - SF36v2, PHQ-9, GAD 7, Mediterranean Diet Score                                                                                             | ✓                                        | ✓                                                   | ✓                                            |
| Care utilisation Monitoring                                                                                               | ✓                                        | ✓                                                   | ✓                                            |
| (Serious) Adverse Events Monitoring                                                                                       | ✓                                        | ✓                                                   | ✓                                            |

1. Routine practice

2. Between T1 (6 months) and T2 (12 months) monitoring of care utilisation and registration of events is done by monthly telephone calls with the participant.

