## 6. TREATMENT OF SUBJECTS

### 6.1 Investigational product/treatment

Patients participating in the *mCR* programme (or intervention group) will undergo 6 months of mobile telemonitoring guidance and in addition another 6 months without mobile telemonitoring. The *mCR* group receives a heart rate monitor and smartphone with a special application to use for their training in their home environment. This smartphone can only be used by the patient for research purposes and will be given back to the researcher once the patient finishes the first 6 months in the study with mobile telemonitoring guidance. Instructions are given to the patient by the researcher, nurse or physician before they start training with a heart rate monitor and smartphone at home. Patients are instructed to exercise while wearing the heart rate monitor at 5 days per week for at least half an hour at an individual selected level of intensity and self-chosen type of activity. The outcomes of the maximal exercise tests on the first visit will enable to personalise the heart rate zones per patient in order to see (after every training/activity) in what zone the patient is training. At the moment patients start an exercise, they need to wear the heart rate monitor, and select on their smartphone the type of activity they are going to perform. While finishing the exercise patients have to register at the smartphone they are done and fill in the rate of perceived exertion (BORG-score). Accordingly, the duration, intensity (based on the heart rate zones) and BORG-score of each training/activity is collected by the smartphone and transferred to a secured website where both patient and researchers/nurses involved in the study can view the results. During the first month patients receive weekly individual coaching and feedback on their training results by telephone, in the second month this will be once per two weeks, whereas one monthly call will be held in the last four months (month 3 until 6) of the mobile telemonitoring period. Mobile telemonitoring guidance will help to improve the self-management skills and stimulate a patient to exercise independently. Besides the coaching by telephone and the advice to train 5 days a week for a minimum of 30 minutes at the start of the first 6 months, there will be no other advices given by the researcher, nurse or physician via the smartphone or secured website. At the end of the first 6 months, the patients are asked to return the heart rate monitor and smartphone to the researcher. In the second period without mobile telemonitoring (month 7 until 12) patients will receive no coaching or feedback by phone. Cardiac patients that are randomised to the control group will undergo 6 months with no *mCR* programme with another 6 months of follow-up in addition. During the study period both groups will receive standard outpatient care and control by a cardiologist. See paragraph 6.2 for more information about the way data are collected by the smartphone in the intervention group.

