#### Secondary study endpoints/outcome

- Difference in  $VO_{2peak}$  from an incremental exercise test (T2-T0, T2-T1)
- Traditional risk factors:
  - Changes in lipid profile (T1-T0, T2-T0, T2-T1)
  - Changes in HbA1C (T1-T0, T2-T0, T2-T1)
  - Changes in renal function (T1-T0, T2-T0, T2-T1)
  - Changes in lean body mass (T1-T0, T2-T0, T2-T1)
  - Changes in blood pressure (T1-T0, T2-T0, T2-T1)
  - Changes in smoking habit (T2-T0)
- MACE: the occurrence of events (cardiovascular (CV) mortality, all-cause mortality, near sudden cardiac death, ACS, CV intervention/surgery, CV hospital admission, CV emergency visits) as composite endpoint (T2-T0) are registered and collected by monthly telephone calls.
- General health:
  - Difference in depression score assessed by: PHQ-9 questionnaire (T1-T0, T2-T0, T2-T1)
  - Difference in anxiety score assessed by GAD-7 questionnaire (T1-T0, T2-T0, T2-T1)
  - Quality of Life: SF-36v2, difference in Physical Component Summary Score and Mental Component Summary Score (T1-T0, T2-T0, T2-T1)
  - Difference in dietary pattern (reflected by total score and score on individual components) assessed by Mediterranean Diet Score (T1-T0, T2-T0, T2-T1)
- Care utilisation as composite endpoint of: (number of) admissions, emergency visits and cardiac interventions (PCI, CABG) (T2-T0).
- Costs of care utilisation based on activities (clinical admission days, emergency and outpatient clinic visits, GP visits for cardiac (related) complaints or issues, radiology/cardiophysiology/nuclear and laboratory tests,

and cardiac interventions) registered at T0, T1 and T2 and collected by monthly telephone calls with the participants between T1 and T2.

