**Information Collection MACE, Care Consumption**

The occurrence of events (MACE (21) [cardiovascular mortality, all-cause mortality, near sudden cardiac death, acute coronary syndrome, CV Intervention/surgery, CV hospital admission, CV emergency visits]) and utilisation of care ((days) admission, outpatient clinic visits, GP visits, interventions, cardiophysiology, radiology, nuclear and lab testing) will be collected by a monthly telephone call with the participants using a standardised schedule throughout the study period. The telephone calls will be performed by a nurse. No advices or support will be given to the participants regarding their daily exercise or lifestyle changes.

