### *Health care cost estimation:*

Direct costs for mobile cardiac rehabilitation will be assigned for the intervention group (with telemonitoring guidance), but not for the control group (no intervention). Care utilization based on activities (clinical admission days, emergency and outpatient clinic visits, GP visits for cardiac (related) complaints or issues, radiology/cardio physiology/nuclear and laboratory tests, and cardiac interventions) will be registered at T1 and T2 and collected by monthly telephone calls with the participants between T1 and T2. A price will be assigned to each service and summed up for each patient individually:

|                                   | Mobile CR | control |
|-----------------------------------|------------------|----------------|
| Costs for CR               | Yes              | No             |
| Costs for care utilization | Yes              | Yes            |

Therefore, total costs (= TC) per patient comprise:

1. Costs for telemonitoring guidance (= CCR, only intervention group)
2. Sum of costs for medical services used outside CR (care utilization, = CCU).

Linear mixed models with centre as random effect will test differences between intervention and control group regarding total costs of care utilisation (see also section 5.1).

Additionally, incremental cost effectiveness ratios (ICER) defined as

$$\frac{\text{Total costs mobile CR} - \text{Total costs control group}}{\text{Outcome mobile CR} - \text{Outcome control group}}$$

will be estimated and a 95% confidence interval will be calculated. Outcome refers especially to the change of peak VO2 and Quality of Life (measured by Physical Component Summary Score and Mental Component Summary Score) during the follow-up period.

[figure not shown]

## 12. Study objective 8

Cardiac patients randomised to the *mCR* programme comply with the use of the smartphone (use of the smartphone on at least 4 days per week with a minimum of 30 minutes of activity per day with a total registration of 150 minutes of activity per week during 21 weeks) during the first 6 months of the study.

Descriptive statistics will be utilised to obtain insight in the use of the smartphone during the first six months of the study. Listed below are the parameters that will be determined.

- Total time (in hours) use of physical activity monitor
- Total time (in hours) use of physical activity monitor with light to moderate intensity

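### The protocol and SAP disagree on whether the monthly event and care-use calls cover months 1-6; if they do not, capture in those months can differ by arm, mainly for items that rely on recall

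*Combined protocol and SAP*

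**What the plan says.** Five statements bear on when events and care use are collected by telephone.

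- Protocol 7.6, on MACE and care consumption, says that both "will be collected by a monthly telephone call with the participants using a standardised schedule throughout the study period". It draws no distinction between arms. A nurse makes the calls and gives no advice on exercise or lifestyle.
- Protocol 7.2.1, MACE bullet: the events "as composite endpoint (T2-T0) are registered and collected by monthly telephone calls". No restriction to the second half-year is stated, so this fits 7.6.
- Protocol 7.2.1, cost bullet, lists the activities to be costed, ending "and cardiac interventions) registered at T0, T1 and T2 and collected by monthly telephone calls with the participants between T1 and T2".
- Protocol Appendix I, footnote 2: "Between T1 (6 months) and T2 (12 months) monitoring of care utilisation and registration of events is done by monthly telephone calls". The footnote is attached both to care utilisation and to (serious) adverse event monitoring.
- SAP 11 says that care utilisation for costing "will be registered at T1 and T2 and collected by monthly telephone calls with the participants between T1 and T2".

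The coaching schedule is a separate matter. Protocol 6.1 states: "During the first month patients receive weekly individual coaching and feedback on their training results by telephone". Calls then become two-weekly in month 2 and monthly in months 3 to 6, and stop after that. The Summary states that controls receive no coaching. Under 7.4 the coach may be a physician, a nurse or a researcher.

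**The concern.** Hypotheses 4 (MACE), 6 (care utilisation) and 7 (costs) are between-arm comparisons, and each needs events and care use to be found equally well in both arms. Sites have two instructions. One gives every patient about six standardised event calls before T1; the other gives none.

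The choice matters most in months 1-6, when the intervention runs and only the mCR arm speaks regularly to study staff. Under 8.2.1, adverse events that a patient mentions spontaneously to site staff are recorded, so a coaching call can act as a reporting route. The trial is open, and 7.5 says that the outcome assessor is not blinded. No section says how an event mentioned during coaching should be handled.

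Without standardised calls before T1, an mCR patient has more chances to report an event, and to report it near its date. This could affect the 6-month MACE-free probability and the Cox model in SAP 8, and the total costs and the ICER numerator in SAP 11. The list of changes in SAP 18 does not mention call timing, so the narrower version does not read as a deliberate change from the protocol.

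**Working it through.** **Step 1. Count the scheduled calls.** The documents state no total, so there is no planned figure to reproduce.

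Coaching calls in mCR, months 1-6 (Protocol 6.1): 4 weekly + 2 two-weekly + 4 monthly = 10. Counting calendar weeks instead, 52/12 + 52/24 + 4 = 10.5. Controls: 0.

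Event and care-use calls: about 6 per half-year in which they run, in both arms.

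| Period | Version | mCR | Control | Difference |
|---|---|---|---|---|
| Months 1-6 | 7.6 (all year) | 10 + 6 = 16 | 6 | 10 |
| Months 1-6 | Appendix I (T1-T2 only) | 10 + 0 = 10 | 0 | 10 |
| Months 7-12 | either | 6 | 6 | 0 |
| 12 months | 7.6 | 22 | 12 | 10 |
| 12 months | Appendix I | 16 | 6 | 10 |

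The difference of 10 comes from the coaching schedule and is the same in both versions. What the contradiction decides is whether both arms have a common set of six standardised event calls before T1, or none.

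**Step 2. Sort the conflict by outcome.**

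- MACE: 7.6 and the 7.2.1 MACE bullet agree. Only Appendix I, footnote 2, departs from them. SAP 8 does not describe collection.
- Care use and costs: 7.6 stands against the 7.2.1 cost bullet, Appendix I, footnote 2, and SAP 11.

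The textual conflict is therefore stronger for costs than for MACE.

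**Step 3. Illustrate the size.** The documents give no capture rates, so those below are assumptions. With no true difference between arms, the apparent ratio is capture in mCR divided by capture in control.

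Months 1-6 only:
- 95% versus 80%: 0.95/0.80 = 1.19
- 95% versus 70%: 0.95/0.70 = 1.36

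Over 12 months, further assuming that events split evenly between the half-years and that capture is 95% in both arms in months 7-12:
- (0.95 + 0.95)/(0.80 + 0.95) = 1.90/1.75 = 1.09
- (0.95 + 0.95)/(0.70 + 0.95) = 1.90/1.65 = 1.15

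The second half-year has equal scheduled calls under either version, so the excess is roughly halved over the full year. Under these assumptions the distortion runs against mCR, because more of its events and care use are found.

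**The case against.** The case on the other side is substantial, and most of it stands.

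*The contradiction does not create the extra contacts.* A reader might infer that mCR has 10 more contacts because the documents disagree. Step 1 shows otherwise: the gap is 10 under either version, and aligning the text does not close it. Alignment adds a common standardised capture route alongside the coaching.

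*Controls are not out of sight.* A reader might take 10 versus 0 to mean that controls have no contact before T1. The documents do not support this. Protocol 6.1 gives both arms routine cardiology outpatient care. Section 8.2.3.1 has the investigator monitor adverse events in every subject, including those found in medical records. The zero refers to scheduled study calls only.

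*Much of the capture is record-based.* Protocol 11.1 builds the eCRF on chart review, with procedure reports and admission and discharge summaries as sources. Section 11.2 has reported endpoints checked, and 8.3 has endpoint events adjudicated. Deaths, admissions and interventions usually leave dated records. This greatly reduces the risk for those items but does not remove it: adjudication and endpoint checks work on events already reported, and care outside the centre can still be missed. GP visits, which are in the cost list but not in the utilisation composite of 7.2.1, are the most exposed.

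*The mechanism is inferred.* No section says that coaching calls collect events or care use; 6.1 describes feedback on training. Spontaneous reporting makes leakage between the two possible, but the documents do not show that it happens.

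**Conclusion.** The contradiction in call timing is plain on the page and needs to be reconciled. Its consequence is conditional: if sites follow Appendix I, months 1-6 have no standardised event calls in either arm, mCR patients have about 10 further occasions to report, and capture can differ by arm. The effect would fall mainly on recall-dependent items and cost components, and much less on deaths, admissions and interventions.

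A stronger conclusion, that all three comparisons are biased, is not supported. The documents give no capture rates and do not show which schedule sites follow. The ratios of 1.19 and 1.36 are illustrations for months 1-6 and should not be read as 12-month effects; the corresponding full-year figures are about 1.09 and 1.15, given an even split of events and equal capture after T1. Confidence is high for the textual conflict and modest for the size of any bias.

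The VO2peak primary analysis and the sample size do not depend on this point. The change is worth making because it protects secondary comparisons at little cost.

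**What to change.** 1. Align the cost bullet of Protocol 7.2.1, Appendix I, footnote 2, and SAP 11 with Protocol 7.6, so that both arms have the same monthly standardised call and the same form in months 1-12.
2. State that event dates are recorded at each call, and that this data collection is kept separate from the coaching calls.
3. Add to the SAP a sensitivity analysis of MACE, utilisation and costs limited to record-verified items (deaths, admissions, interventions). Because the coaching contacts remain after alignment, this analysis is useful under either version. It is also the main protection for any patient who has already passed T1 without the calls.

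Cost: wording in three places, a short statement on dates and on separation from coaching, and one small extra analysis. At sites that followed Appendix I it means up to six short calls per patient. Section 7.6 already requires these calls, so no new procedure is added.

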**A. INTRODUCTION**

1. The World Medical Association (WMA) has developed the Declaration of Helsinki as a statement of ethical principles for medical research involving human subjects, including research on identifiable human material and data.

The Declaration is intended to be read as a whole and each of its constituent paragraphs should be applied with consideration of all other relevant paragraphs.

2. Consistent with the mandate of the WMA, the Declaration is addressed primarily to physicians. The WMA encourages others who are involved in medical research involving human subjects to adopt these principles.

